**Figure 1 F1:**
[figure not shown]
Participation process. HSCPs, health and/or social care providers.

### Measurements

All measurements can be found in online supplemental appendix 1. All consortium partners agreed on the content, and measurements were translated into the languages of the platform, either by human translators following current ISO standards or by using Microsoft Translator for automatic translations that were carefully checked/corrected by native speakers. The questionnaires and platform all start by filling out a personalised code in order to link the surveys to platform usage. Only the principal and executive investigators at the university in a participant’s country of residence will be able to link a personal code to a participant’s identity.

#### Primary outcome measurements

In line with RQ1, the main study parameter is access to mental healthcare services, measured by means of four dimensions, that is, availability, approachability, acceptability and appropriateness.^37 38^ These four dimensions are the main endpoints for this study. Based on other existing questionnaires, we selected and/or developed our own questions to assess these dimensions. In particular, we used existing scales for mental health literacy,^45^,^47^ and the Canadian Community Health Survey on accessibility, acceptability and availability^48^ as inspiration for these endpoints. Additionally, we supplemented the dimensions with statements that were considered of particular relevance in the current context (ie, migrants/refugees and mental health) based on the extensive expertise of the project team. These primary outcome measurements will be assessed at T0 (pre test), T2 (first post test) and T3 (second post test).

*Availability of care*: the presence and capacity of facilities will be assessed with five items on a five-point Likert scale (1=strongly disagree, 5=strongly agree).*Approachability of care*: this dimension entails access to information on (patient) rights, services available and costs of services and will be assessed with seven items on a five-point Likert scale (1=strongly disagree, 5=strongly agree).*Acceptability of care*: this dimension assesses providers’ cultural competence and will be assessed with four items on a five-point Likert scale (1=strongly disagree, 5=strongly agree).*Appropriateness of care*: this dimension indicates how well the services provided match the needs of the refugee/migrant populations and will be assessed with six items on a five-point Likert scale (1=strongly disagree, 5=strongly agree).

#### Secondary outcome measurements

The secondary study parameters are related to the process evaluation of the platform (RQ2 and RQ3), in particular, the animated videos and the resource repository/information portal and the HSCP training, which will be measured at T2 (first post test) and at T1a (by tracking the actual usage of the digital platform). The secondary endpoints for this study are:

*Actual usage of the digital platform*: we will monitor participants’ actual usage of the platform by means of a built-in tracker. In particular, we will collect data on the time spent in total and on each separate page, the number of visits, the number of clicks and the videos that were watched.^49^ Each participant will receive a unique personal code to log into the digital platform. This will enable us to connect website usage to other outcomes from the surveys.*Ease of use*: inspired by the Extended Unified Theory of Acceptance and Use of Technology (UTAUT2),^50 51^ we will use the three items of the ‘effort expectancy’ subscale to measure the ease of use of the digital platform. For ease of administration (especially when the surveys have to be verbally administered by a research assistant) and consistency, we will assess all items on a five-point Likert scale (1=strongly disagree, 5=strongly agree), rather than the original seven-point Likert scale.*Usefulness of the content*: inspired by the UTAUT2,^50 51^ we will use two items from the ‘performance expectancy’ subscale to measure the usefulness of the digital platform. For ease of administration (especially when the surveys have to be verbally administered by a research assistant) and consistency, we will assess all items on a five-point Likert scale (1=strongly disagree, 5=strongly agree), rather than the original seven-point Likert scale.*Comprehensibility of the information*: we will use the three items from the subscale ‘satisfaction with comprehensibility’ of the Website Satisfaction Scale.^52^,^54^ For ease of administration (especially when the surveys have to be verbally administered by a research assistant) and consistency, we will assess all items on a five-point Likert scale (1=strongly disagree, 5=strongly agree), rather than the original seven-point Likert scale.*Attractiveness of the content*: we will use the five items from the subscale ‘satisfaction with attractiveness’ of the Website Satisfaction Scale.^52^,^54^ For ease of administration (especially when the surveys have to be verbally administered by a research assistant) and consistency, we will assess all items on a five-point Likert scale (1=strongly disagree, 5=strongly agree), rather than the original seven-point Likert scale.*Emotional support*: We will use the four items from the subscale ‘satisfaction with emotional support’ of the Website Satisfaction Scale.^52^,^54^ For ease of administration (especially when the surveys have to be verbally administered by a research assistant) and consistency, we will assess all items on a five-point Likert scale (1=strongly disagree, 5=strongly agree), rather than the original seven-point Likert scale.

#### Other (control) measurements

For all participants, the baseline/pretest questionnaire (T0) will include sociodemographic items that inquire about participants’ age, gender, education level, native country and country of residence. For the HSCPs, we will ask additional questions about their working and postgraduate training experiences, in particular with migrants and refugees. For migrants and refugees, we will ask about the main reason for leaving their native country and how long they have been living in their current country of residence. Furthermore, we will measure the following potentially confounding factors at T0 (pre test):

*Mental health status* (only for LLP migrants/refugees): we will use the Mental Health Inventory-5 (MHI-5) to measure participants’ mental health status,^55^ which is part of the Short Form 36-Item Health Survey (SF-36).^56^ The MHI-5 consists of five items, which we will assess on a five-point scale (1=none of the time, 5=all of the time).*Health literacy*: the ability to perform the basic reading and numerical tasks required to function in the healthcare environment will be assessed using the set of brief screening questions (SBSQ).^57^ The SBSQ consists of three items on a five-point scale (1=never/not at all confident, 5=always/extremely confident).*eHealth literacy*: using the eHealth Literacy Scale (eHEALS),^58^ we will measure participants’ knowledge, comfort and perceived skills at finding, evaluating and applying electronic health information to health problems. The eHEALS consists of eight items on a five-point Likert scale (ie, 1=strongly disagree, 5=strongly agree).*Language proficiency in the main country of residence’s language*: we will ask participants to rate their proficiency in the main language of their country of residence using four items (ie, speaking, listening, reading and writing) on a five-point scale (ie, 1=not at all fluent, 5=completely fluent).

At T2 (first post test), we will measure the following parameters for all participants:

*Technology acceptance*: in order to measure participants’ general acceptance of health websites, we will use two items from the ‘performance expectancy’ subscale, and the subscales ‘effort expectancy’ and ‘behavioural intention’ of the UTAUT2,^50 51^ totalling to eight items. For ease of administration (especially when the surveys have to be verbally administered by a research assistant) and consistency, we will assess all items on a five-point Likert scale (1=strongly disagree, 5=strongly agree), rather than the original seven-point Likert scale.*Language proficiency in the platform language*: we will ask participants to rate their proficiency in the language in which they used the multilingual digital platform using four items (ie, listening and reading) on a five-point scale (ie, 1=not at all fluent, 5=completely fluent).

The questionnaire at T2 (first post test) will also include some open-ended questions on the digital platform (ie, what participants liked and disliked, what they think could be added to the platform and other comments/thoughts on the platform). At T3 (second post test), additional open-ended questions will be asked on how HSPCs and migrants/refugees have used the intervention in practice.

### Sample size calculation

Based on an a priori power analysis using G*power V.3.1, with effect size set at f2 of 0.2, p value of <0.05 and power of 0.80 and number of groups and measurements at 2 (Analysis of Variance/ANOVA, repeated measures within subjects), a sample size of n=52 is required. Therefore, we will sample at least 52 HSCPs across all nine consortium countries. Additionally, we strive to include around five times as many LLP migrants and refugees (n=260) to ensure more diverse representation of migrants across different European countries and to ensure sufficient power for, for example, sensitivity analyses and including relevant covariates. In each country, we aim to include about 6–10 HSCPs and 30–35 migrants and refugees (to account for possible dropout).

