### Statistical analysis

The latest version of IBM SPSS Statistics will be used to statistically analyse the data. The data analysis will be performed by researchers from the project lead of this work package, that is, the University of Amsterdam. For the analysis of the primary endpoints, that is, the four dimensions of access to mental healthcare, we will perform one-sided t-tests and repeated measure ANOVAs to evaluate differences in the measurements between the pre test (baseline survey) and post tests per group of participants (ie, migrants/refugees and HSCPs separately). Additionally, we will perform ANOVAs to check for possible covariates. If possible, we will perform sensitivity analyses with only the migrants/refugees who are currently experiencing self-reported mental health issues and explore differences between the participating countries. We will use a significance level of p≤0.05 for all analyses. Descriptive statistics will be provided for the secondary endpoints. Additionally, descriptive statistics and frequency distributions will also be generated for the participants’ sociodemographics.

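### The required n of 52 does not follow from the stated effect size f2 = 0.2; it fits f = 0.2 (f2 = 0.04), so the effect size is most likely mislabelled

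*Protocol article*

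**What the plan says.** The section Sample size calculation reports a G*Power 3.1 calculation for "Analysis of Variance/ANOVA, repeated measures within subjects". Its inputs are given as "with effect size set at f2 of 0.2, p value of <0.05 and power of 0.80 and number of groups and measurements at 2". From these it concludes that "a sample size of n=52 is required". That number becomes the minimum for health and social care providers (HSCPs), and the migrant target of 260 is set at about five times it. The article gives no pre-post correlation.

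The section Statistical analysis says of the primary endpoints that "we will perform one-sided t-tests and repeated measure ANOVAs", with migrants and HSCPs analysed separately.

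**The concern.** In this test family G*Power takes Cohen's f, and f2 is its square. An f2 of 0.2 means f = 0.447, a large within-subject effect, for which 52 is far more than 80% power requires. An f of 0.2 is a much smaller effect. The two readings differ fivefold in f2 (0.20 against 0.04) and about 2.2-fold in f (0.447 against 0.20).

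This is the only power statement in the article. It supports the HSCP minimum directly and the migrant target by multiplication. As printed, it tells the reader that the study was planned around a change more than twice as large as the one n = 52 appears to be designed for.

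**Working it through.** **Inputs.** From Sample size calculation: within-subjects repeated-measures ANOVA, f2 = 0.2, alpha 0.05, power 0.80, k = 2 groups, m = 2 measurements, stated N = 52. Not stated: the correlation rho between the measurements. I take rho = 0.5 as the base assumption and vary it.

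**Formula.** Noncentral F with

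- lambda = N × m × f2 / (1 − rho)
- df1 = m − 1 = 1
- df2 = (N − k)(m − 1) = N − k

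**Step 1: the stated inputs, f2 = 0.2.** At N = 52 and rho = 0.5, lambda = 52 × 2 × 0.2 / 0.5 = 41.6, and power exceeds 0.999. The smallest N for 80% power is 12 with one group (power 0.805). With two groups it is 13 (0.835; N = 12 gives 0.797), or 14 if the groups are equal (0.866).

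**Step 2: can another correlation rescue 52?** Still at f2 = 0.2:

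| rho | lambda at N = 52 | Power at N = 52 | Required N |
|---|---|---|---|
| 0.5 | 41.6 | > 0.999 | 12 to 14 |
| 0.3 | 29.7 | > 0.999 | 16 |
| 0 | 20.8 | 0.994 | 22 |
| towards −1 | 10.4 | about 0.885 | about 42 |

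Required N rises as rho falls. Since rho cannot go below −1, about 42 is the ceiling, and no admissible correlation gives 52.

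**Step 3: other settings at f2 = 0.2.** None gives 52:

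- G*Power's alternative effect-size conventions: 43 to 44 (as in SPSS) and 42 (as in Cohen).
- The between-factor test: 22 to 38 for rho from 0 to 0.8.
- Three measurements with rho = 0.5: 10.
- Alpha 0.10 (the one-sided equivalent) with rho = 0.5: 10.

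**Step 4: read the effect size as f = 0.2, so f2 = 0.04.** With rho = 0.5, lambda = 52 × 2 × 0.04 / 0.5 = 8.32. Power at N = 52 is 0.8075 with two groups and 0.8078 with one. At N = 51 with two groups it is 0.7996. So 52 is exactly the required number, for one group or two.

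**Step 5: the size of effect.** With two measurements the standardised change is 2f, and at rho = 0.5 this equals the paired effect size dz. For f = 0.2 it is 2 × 0.2 = 0.40; for f2 = 0.2 it is 2 × 0.447 = 0.89. As a cross-check, a two-sided paired t-test with dz = 0.40 also needs 52.

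**Step 6: sidedness.** The F test does not distinguish direction, so 52 corresponds to a two-sided test at 0.05. A one-sided paired t-test at 0.05 with dz = 0.40 needs 41.

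**The case against.** The strongest reply is that this is a slip of notation. Writing f for f2 recovers 52 exactly, and nothing in recruitment, participant burden or analysis then changes. That stands, and it limits the point to a correction of the stated input. A reader might infer that the study is underpowered, or that 52 is the wrong number. The article does not support either reading: at f = 0.2 and rho = 0.5 both 52 and 80% power hold, and at f2 = 0.2 there would be more power than claimed.

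A reader might also treat the two-group input as a separate fault, taking 52 as 26 in each group. It changes no number, because one group also gives 52, and the article applies 52 to HSCPs alone. Only the description of the input fails to match the separate analysis.

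Nor is the missing correlation an error in itself, since a condensed article may leave it to the full protocol. It matters here only because the exact match at f = 0.2 depends on it. With one group, rho = 0.3 would need 71 and rho = 0.7 would need 32.

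Finally, the article does not use the planning effect as a threshold for success; it judges results at p≤0.05. It would go too far to say that a null HSCP result will be misjudged.

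One caution runs the other way. Multiple regression with two predictors also gives 52 at f2 = 0.2 (power 0.806). The article names a repeated-measures ANOVA, so this does not rescue the sentence. It is, however, a reason to look at the saved output before relabelling anything.

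**Conclusion.** The statement is wrong as written. That 52 is not the required N at f2 = 0.2 under the named test holds for every admissible correlation. The more specific conclusion, that f = 0.2 was entered and misreported as f2, rests on the assumed rho = 0.5 and is very likely but not proven. On that reading the target standardised change is about 0.40 where the printed value implies about 0.89, and the sample size and the 80% power both stand. It is a mislabelled input in the only power statement, not a deficiency in the size of the study.

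**What to change.** Check the saved G*Power output. If it confirms the likely reading, restate the effect size as f = 0.20 (f2 = 0.04), give the correlation that was actually entered, and describe the calculation as one group of HSCPs analysed separately. If the output shows a different test or effect size, correct the sentence to match it.

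Also state that 52 refers to the non-directional F test at 0.05, and reconcile this with the one-sided t-tests in Statistical analysis, for which 41 would suffice under the same assumptions.

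The cost is one or two sentences. If the output confirms f = 0.2, recruitment targets do not change.

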### Statistical analysis

The latest version of IBM SPSS Statistics will be used to statistically analyse the data. The data analysis will be performed by researchers from the project lead of this work package, that is, the University of Amsterdam. For the analysis of the primary endpoints, that is, the four dimensions of access to mental healthcare, we will perform one-sided t-tests and repeated measure ANOVAs to evaluate differences in the measurements between the pre test (baseline survey) and post tests per group of participants (ie, migrants/refugees and HSCPs separately). Additionally, we will perform ANOVAs to check for possible covariates. If possible, we will perform sensitivity analyses with only the migrants/refugees who are currently experiencing self-reported mental health issues and explore differences between the participating countries. We will use a significance level of p≤0.05 for all analyses. Descriptive statistics will be provided for the secondary endpoints. Additionally, descriptive statistics and frequency distributions will also be generated for the participants’ sociodemographics.

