**Methods and analysis:**

We will conduct a pretest–post-test cross-national survey study to evaluate the platform’s effect evaluation (primary objective) and process evaluation (secondary objective). The primary outcomes (measured at T0, T2 and T3) are four dimensions of access to mental healthcare services: availability, approachability, acceptability and appropriateness of mental healthcare. Secondary outcomes (measured at T2) are: actual usage of the platform (ie, tracking data), perceived ease of use, usefulness of content, comprehensibility of information, attractiveness of content and emotional support. Participants will be recruited from nine European countries: Belgium, Germany, Italy, Lithuania, the Netherlands, Poland, Slovakia, Spain and the UK. Using convenience sampling through professional networks/organisations and key figures, we aim to include at least 52 HSCPs (ie, 6–10 per country) and 260 LLP migrants (ie, 30–35 per country). After completing a pretest questionnaire (T0), participants will be requested to use the platform, and HSCPs will participate in an additional personalised training (T1). Next, participants will fill out a post-test questionnaire (T2) and will be requested to participate in a second post-test questionnaire (T3, about 6–8 weeks after T2) to answer additional questions on their experiences through a brief phone interview (T3 is optional for migrants/refugees).

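### Four main endpoints are each tested at p≤0.05 in each participant group, with no adjustment, primary post-test or success rule: about a 12–19% chance of a false positive per group at one post-test

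*Protocol article*

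**What the plan says.** All four dimensions of access have equal rank. Primary outcome measurements states: "These four dimensions are the main endpoints for this study". On timing, the same section adds: "These primary outcome measurements will be assessed at T0 (pre test), T2 (first post test) and T3 (second post test".

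Statistical analysis gives the tests for these endpoints: "we will perform one-sided t-tests and repeated measure ANOVAs to evaluate differences in the measurements between the pre test (baseline survey) and post tests". They are run "per group of participants (ie, migrants/refugees and HSCPs separately". One error rule covers everything: "We will use a significance level of p≤0.05 for all analyses".

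The Sample size calculation plans a single test, with "p value of <0.05 and power of 0.80 and number of groups and measurements at 2", and arrives at n=52 for HSCPs. Migrants/refugees are set at about five times that number (260). For migrants the last measurement is not compulsory; the Abstract notes that "T3 is optional for migrants/refugees".

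No section ranks the dimensions or the post-tests, chooses between the t-test and the ANOVA, or says how many dimensions must change for the platform to count as effective.

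**The concern.** Each main endpoint gets its own full 5% error rate. In one group there are four chances of a false finding at one post-test, and eight if T2 and T3 are both compared with T0. RQ1 asks about all four dimensions together, so a reader will look at the set, and one significant result in the set can be reported as an effect of the platform.

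This has consequences. The Abstract (Ethics and dissemination) makes public release depend on success, and the Intervention section ties open access to positive results. Neither defines those words. Because there is no control group, the answer to RQ1 rests on these pre–post tests.

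The point concerns a rule the article states, not a detail it leaves out. An SAP that adjusted over the four endpoints would contradict the sentence that sets one level for every analysis.

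**Working it through.** **Inputs from the protocol article.** Four main endpoints; two groups analysed separately; post-tests T2 and T3; one-sided t-tests and repeated-measures ANOVAs; level 0.05 throughout; effect size 0.2, power 0.80, n=52 (HSCPs) and n=260 (migrants).

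**Assumptions, because the article gives no figures.** Correlation between dimensions 0, 0.5 or 0.7; correlation between the T2 and T3 changes 0.5; pre–post correlation 0.5.

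**1. The plan's own figure.** For a within-subject repeated-measures ANOVA, λ = f²·N·m/(1−ρ). Reading 0.2 as f, with m=2 and ρ=0.5:
- λ = 0.04 × 52 × 2 / 0.5 = 8.32 on 1 and 50 degrees of freedom.
- Power is 0.807, and 52 is the smallest N that reaches 0.80, so n=52 is reproduced.
- This equals a paired change of 2f/√(2(1−ρ)) = 0.4 SD.

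The article writes the effect size as f2. Read literally (f = √0.2 = 0.447, same ρ), the required N would be 13. The power figures in step 4 therefore depend on reading 0.2 as f.

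**2. One group, one post-test (four tests).** With no true effect and independent dimensions, 1 − 0.95⁴ = 0.185. A multivariate normal simulation (1,000,000 draws) covers the correlated cases:

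| Correlation between dimensions | One-sided 0.05 | Two-sided 0.05 |
|---|---|---|
| 0 | 18.6% | 18.6% |
| 0.5 | 14.4% | 15.6% |
| 0.7 | 12.1% | 13.0% |

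The two-sided column also applies to a T0–T2 ANOVA, which with two measurements is equivalent to the two-sided paired t-test.

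**3. One group, both post-tests (eight tests).** With one-sided tests and T2–T3 correlation 0.5, the chance is 30.8%, 23.8% and 20.1% at between-dimension correlations 0, 0.5 and 0.7. These figures leave out the parallel ANOVAs and the covariate, country and subgroup tests.

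**4. Effect of adjustment on power.** Bonferroni, which is also the first Holm step, uses 0.05/4 = 0.0125. If all four tests are independent, the family-wise error is then 1 − 0.9875⁴ = 0.049. For n=52 and a 0.4 SD change (noncentral t; Holm by simulation with all four dimensions changing by 0.4 SD and between-dimension correlation 0 to 0.7):

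| Test | Unadjusted 0.05 | At 0.0125 | Holm, average per dimension |
|---|---|---|---|
| Two-sided paired t, or ANOVA | 0.81 | 0.62 | about 0.70–0.73 |
| One-sided paired t | 0.89 | 0.72 | about 0.80–0.84 |

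At n=260, power at 0.0125 is above 0.999 with either test.

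**The case against.** **Multiplicity procedures are often left to the SAP.** That is true in general, but here the article fixes the level for every analysis, so the objection does not remove the point.

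**Each dimension may be its own question.** RQ1 lists the four separately, and the Intervention section links each to its own platform component (map, migrant videos, HSCP videos, repository). Dimension-by-dimension reporting without a joint claim would be defensible. However, the article does not say that its conclusions will be kept separate, and it speaks of success for the platform as a whole.

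**A reader might infer an overall error of about 50%.** Sixteen tests (four dimensions, two groups, two post-tests) give 52%, 42% and 36% at between-dimension correlations 0, 0.5 and 0.7, with T2–T3 correlation 0.5. The documents do not support this as the headline. The groups are analysed separately, T3 is optional for migrants, and the Procedures section describes T3 for HSCPs only. An omnibus ANOVA over all time points would also give just four tests per group.

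**A reader might infer that the 80% power is wrong.** It is not. Power per endpoint is conventional. If the one-sided t-test is chosen, average Holm power per dimension stays at about 0.80 or higher. All that is missing is a statement of what the 80% covers.

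**A reader might infer that one chance result would trigger release.** The article does not say this. If all four dimensions had to be significant there would be no inflation, but that rule is not stated either.

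**Conclusion.** The concern holds at the level of one participant group. Four equally ranked main endpoints at unadjusted 0.05 give about a 12–19% chance of at least one false positive at a single post-test, and about 20–31% if both post-tests are tested. The first range is the firmer one: it needs neither pooling of the groups nor any T3 data, and even at correlation 0.7 it is more than twice the nominal 5%.

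The figures assume one-sided tests, the correlations stated above, and that any one significant dimension is taken as an effect. The article gives no correlations and no success rule, so the last condition is a possibility it leaves open, not something it declares.

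This is a should-fix. The study is uncontrolled and uses convenience sampling, migrant power is unaffected by adjustment, and the correction is small.

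**What to change.** In Statistical analysis, replace the blanket level for the primary endpoints with wording such as:

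> Within each participant group, the primary comparison is T0–T2 on the four dimensions, using one pre-specified test (the one-sided paired t-test or the repeated-measures ANOVA), with Holm's procedure over the four dimensions at 5%. T3, covariate, country and subgroup tests are secondary or exploratory.

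The authors must choose the test before seeing results. T0–T2 matches the two measurements in the sample size calculation and does not depend on the optional T3.

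In Sample size calculation, state that the 80% power is for one dimension at unadjusted 0.05, and add the HSCP power under Holm for the chosen test: about 0.70–0.73 on average per dimension for the ANOVA or two-sided test, or about 0.80–0.84 for the one-sided t-test. State with it the assumptions of a 0.4 SD change (0.2 read as f) and a pre–post correlation of 0.5.

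The cost is a few sentences and somewhat lower stated power for HSCPs. No participants or data are added.
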